# The quantity-effect relationship and physiological mechanisms of different acupuncture manipulations on posterior circulation ischemia with vertigo: study protocol for a randomized controlled trial

**DOI:** 10.1186/s13063-015-0660-y

**Published:** 2015-04-11

**Keywords:** Acupuncture, Quantity-effect relationship, Vertigo

## Abstract

**Background:**

Recent experiments have demonstrated that different needling manipulations may induce variable effects via diverse physiological mechanisms. A previous study indicated that needling at Fengchi (GB 20) improved cerebral blood flow in patients with vertigo induced by posterior circulation ischemia (PCI). In this study, we aim to explore the quantity-effect relationship and the physiological mechanisms underlying different acupuncture manipulations in PCI patients with vertigo.

**Methods/Design:**

We propose a pragmatic randomized and controlled trial. All participants, outcome assessors, and statisticians will be blinded. A total of 144 eligible participants will be randomized into one of four treatment groups receiving acupuncture at Fengchi (GB 20) with different one-minute manipulation parameters. Group 1 will receive twirling at a frequency of 60 times per minute toward the contralateral outer canthus at a depth of 0.5 to 0.8 cun. Group 2 will receive twirling at a frequency of 60 times per minute toward the Adam’s apple at a depth of 0.5 to 0.8 cun. Group 3 will receive twirling at a frequency of 120 times per minute toward the contralateral outer canthus at a depth of 0.5 to 0.8 cun. Group 4 will receive twirling at a frequency of120 times per minute toward the Adam’s apple at a depth of 0.5 to 0.8 cun. Additional points will be added based on individualized pattern diagnoses. The participants will receive 14 acupuncture sessions over 3 to 4 weeks. The subjects will be assessed at two time points: baseline and post-treatment. The primary outcome measurements will include subjective measurements (Vertebrobasilar System Ischemic Neurological Impairment Scale, UCLA Dizziness Questionnaire, Activities of Daily Living Scale, and Psychological and Social Adaptation Scale) and objective measurements (Transcranial Doppler, carotid ultrasonography and changes in cerebral oxygenation) to reduce bias arising from the placebo effect. We will use metabolomics to investigate the mechanisms underlying the different manipulation parameters.

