### Outcome measurement

Outcome measurements will be assessed at baseline and after the treatment phase. We will use multiple outcome measurements, including subjective and objective parameters.

The patients will be required to complete several subjective questionnaires before and after treatment, including the following: the Vertebrobasilar System Ischemic Neurological Impairment Scale (VBS-INIS) (range: 0 to 22) [17], UCLA Dizziness Questionnaire (UCLA-DQ) (range: 5 to 25) [18], Activities of Daily Living Scale (ADL) (range: 14 to 56) [19], and Psychological and Social Adaptation Scale (range: 0 to 20) [20]. All scales have been validated in previous studies.

The VBS-INIS assesses the degree of neurological impairment caused by vertebrobasilar ischemia. Common signs and symptoms include dizziness, deafness or tinnitus, double vision, dysarthria, or swallowing impairment. The scale was demonstrated to be uniform, stable, and reliable. Higher scores indicate more severe damage.

The UCLA-DQ is used to measure the severity and frequency of dizziness. The questionnaire contains five items to evaluate the patients in terms of daily activity, quality of life, and their fear of dizziness.

The ADL is a validated questionnaire that has been widely used to assess ability of an individual to function in daily life. The questionnaire consists of two parts: the Physical Self-Maintenance Scale and the Instrumental Activities of Daily Living Scale.

The Psychological and Social Adaptation Scale mainly describes the impact of dizziness on daily life and work. The scale assesses psychological parameters, such as temper, worry, fear, quality of sleep, and communication with others. The reliability, availability, and sensitivity of this scale had been clinically tested [20].

Objective parameters will also be used to compare differences in cerebral blood flow via TCD and carotid ultrasonography. Changes in cerebral oxygenation will be investigated using near-infrared spectroscopy, and the inherent mechanism underlying acupuncture treatment efficacy will be investigated using metabolomics (Figure 2).

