**Figure 2 Fig2:**
[figure not shown]
Study sequence. A total of 144 eligible participants will be randomized into one of four treatment groups receiving acupuncture for one minute with different manipulation parameters. Group 1 will receive twirling with a frequency of 60 times per minute toward the contralateral outer canthus at a depth of 0.5 to 0.8 cun. Group 2 will receive twirling with a frequency of 60 times per minute toward the Adam’s apple at a depth of 0.5 to 0.8 cun. Group 3 will receive twirling with a frequency of 120 times per minute toward the contralateral outer canthus at a depth of 0.5 to 0.8 cun. Group 4 will receive twirling with a frequency of 120 times per minute toward the Adam’s apple at a depth of 0.5 to 0.8 cun. The participants will receive 14 acupuncture sessions over 3 to 4 weeks. The subjects will be assessed at two time points: baseline and post-treatment. The primary outcome measurements will include subjective measurements (Vertebrobasilar System Ischemic Neurological Impairment Scale, UCLA Dizziness Questionnaire, Activities of Daily Living Scale, and Psychological and Social Adaptation Scale) and objective measurements (Transcranial Doppler, carotid ultrasonography, and changes in cerebral oxygenation) to reduce bias arising from the placebo effect. We will use metabolomics to investigate the mechanisms underlying the effects of the different manipulation parameters.

Certain medical assessments, such as general information, vital signs, symptoms, physical signs, previous history, complications, and information from the TCM diagnosis, will also be recorded.

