#### Analysis strategy

Statistical analysis will be performed using the statistical software package SPSS 16.0 for Windows (SPSS Inc., Chicago, IL, USA). Differences between the baseline characteristics of each treatment group will be analyzed using an analysis of variance (ANOVA) for continuous variables such as age, body mass index, and disease course. Comparisons among the baseline characteristics of the four groups for categorical variables, such as gender and medical history, will be made using the chi-square test. Paired sample *t*-tests will be used to compare the subjective and objective outcome measurements before and after treatment. Comparisons of the subjective and objective outcome measurements among the four groups will be performed by ANOVA. A *P* value of less than 0.05 will be considered statistically significant. Qualified statisticians will perform the statistical analyses in a blinded manner.

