### Trial status

The trial had finished the recruitment phas in August 2014.We will report the results in later article.

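### Seven measurements are all declared primary and compared at P < 0.05 with no order, correction or joint-success rule, so the false-positive rate for the primary claim exceeds 5% (30% if the outcomes are independent and any one suffices)

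*Protocol article*

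**What the plan says.** The abstract (Methods/Design) states: "The primary outcome measurements will include subjective measurements (Vertebrobasilar System Ischemic Neurological Impairment Scale, UCLA Dizziness Questionnaire, Activities of Daily Living Scale", followed by the Psychological and Social Adaptation Scale and then "objective measurements (Transcranial Doppler, carotid ultrasonography and changes in cerebral oxygenation) to reduce bias arising from the placebo effect". That is four questionnaires and three instrument-based measurements. The Figure 2 legend gives the same seven, again as primary and unranked, ending with "objective measurements (Transcranial Doppler, carotid ultrasonography, and changes in cerebral oxygenation) to reduce bias arising from the placebo effect". The Outcome measurement section says "We will use multiple outcome measurements, including subjective and objective parameters" and singles none out.

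The Analysis strategy then says: "Comparisons of the subjective and objective outcome measurements among the four groups will be performed by ANOVA". It sets one threshold, a P "value of less than 0.05 will be considered statistically significant". Paired t-tests on the same outcomes are planned as well: these "tests will be used to compare the subjective and objective outcome measurements before and after treatment". The Sample size section gives 36 per group, 144 in all, with allowance for 20% withdrawal, and names no outcome as its basis. It therefore does not reveal which outcome is meant to carry the trial.

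**The concern.** A trial with several primary outcomes needs a rule that turns the separate results into one conclusion: a single lead outcome, a testing order, an adjusted threshold, or a requirement that all succeed. The article has none of these. It names seven primaries and gives each the full 0.05. Read as written, one significant ANOVA out of seven could be reported as a positive primary result. The trial also aims to find which needling settings work best, so one chance result on one scale or scan could be taken as evidence that direction or frequency matters.

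Seven is also a minimum. TCD, carotid ultrasonography and oxygenation are named as modalities, with no vessel or parameter chosen. If a modality supplies more than one variable, there are more opportunities for a false positive.

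**Working it through.** **Inputs from the article**
- Primary measurements: 4 scales + 3 instrument-based measurements = 7 (abstract; Figure 2 legend).
- Test: four-group ANOVA on each outcome, P < 0.05 (Analysis strategy).
- Size: 4 × 36 = 144, which agrees with the stated total. After 20% withdrawal, 36 × 0.8 = 28.8, about 29 evaluable per group (Sample size).

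The only error rate stated is 0.05 per test, so there is no family-wise figure to reproduce.

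**Assumptions, not in the article**
- One overall F test per measurement.
- Success means significance on at least one of the seven.
- No true difference between groups on any outcome.
- Correlations between outcomes, which are varied over a range.

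**Independent outcomes**

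Family-wise rate = 1 − (1 − 0.05)^7 = 1 − 0.698 = 0.302, or 30%. Whatever the dependence, the rate cannot exceed 7 × 0.05 = 0.35.

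**Correlated outcomes**

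Seven multivariate-normal outcomes were simulated, each tested by a four-group F test at 0.05, with 40,000 replicates per setting. The Monte Carlo standard error is at most √(0.3 × 0.7 / 40,000) = 0.0023, about 0.2 percentage points.

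| Common correlation | 29 per group | 36 per group |
|---|---|---|
| 0 | 30.1% | 30.0% |
| 0.3 | 27.5% | 27.6% |
| 0.5 | 24.0% | 23.5% |
| 0.6 | 21.7% | 21.8% |
| 0.7 | 18.6% | 18.8% |
| 0.8 | 15.5% | 15.6% |
| 0.9 | 11.9% | 12.1% |

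A uniform correlation between questionnaires and blood-flow measures may be unrealistic, so block structures were also tried at 29 per group. With correlations within scales / within instruments / between the two sets of 0.5/0.3/0.1, 0.6/0.4/0.1, 0.7/0.5/0.2 and 0.8/0.8/0.2, the rates are 27.4%, 25.9%, 24.2% and 20.8%.

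**More than one variable per instrument (illustration)**

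If each of the three instruments supplied two variables, there would be 4 + 6 = 10 tests, and 1 − 0.95^10 = 0.401 under independence.

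**With correction**

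Bonferroni across seven uses 0.05/7 = 0.0071 per outcome. The family-wise rate is then at most 7 × 0.0071 = 5%, and 1 − (1 − 0.00714)^7 = 4.9% if the outcomes are independent. Holm keeps the same 5% bound with less loss of power.

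**The case against.** The strongest reply has three parts.

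First, the article states no rule by which any one outcome suffices. If all seven had to be significant, there would be no inflation. This stands to the extent that the percentages are conditional. But the article states no joint-success rule either, and a bare threshold on each primary is most naturally read as seven separate chances.

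Second, the trial describes its purpose as exploring a relationship, and multiplicity details are often left to an analysis plan that is not shown. The exploratory language is real. However, the article itself labels these outcomes primary and fixes an unadjusted threshold, so the rule is stated and is unsuitable. It is not merely absent. An analysis plan that ranked or adjusted the seven would have to override the article.

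Third, correlation between outcomes lowers the rate. That is correct. Below about 20% requires all seven to correlate at roughly 0.65 or more, scales with scans included, and even at 0.9 the rate is more than twice nominal.

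Several stronger readings are tempting but not supported:
- A reader might add the paired t-tests to the count and obtain a far larger error rate. The article does not say these are run separately in each group, and they test change over time. All arms receive real acupuncture, so such change could occur with no difference between groups.
- A reader might include metabolomics. It lies outside the list of primaries and is not named among the tests in the Analysis strategy.
- A reader might reject the placebo rationale outright. The Discussion argues that objective measures are less open to expectation. That is a reason for including such measures, though not for testing all seven without adjustment.
- Because "The trial had finished the recruitment phas in August 2014", a reader might infer that the primary can still be picked after seeing the data. The trial was registered in November 2012, and neither the registry entry nor any analysis plan is at hand. Either may have fixed an outcome or an order, and the statisticians are described as blinded.

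**Conclusion.** The concern holds in a conditional form. The article declares seven co-equal primaries and applies an unadjusted 0.05 to their between-group ANOVAs, with no ordering, correction or joint-success rule. If any one significant result counts and each measurement has one F test, the family-wise false-positive rate is 30% under independence, about 22-28% for common correlations of 0.3-0.6, and 12-19% for 0.7-0.9, against 5%. The count, the test and the threshold come from the article; the correlations and the any-one-suffices reading are assumptions. The excess over 5% persists at every correlation tried, and it grows if an instrument contributes several variables. It hardly depends on whether 29 or 36 per group are analysed.

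**What to change.** Before outcome data are analysed by group:

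1. Fix one variable each for TCD, carotid ultrasonography and cerebral oxygenation, so that the family is exactly seven tests.
2. Apply Holm or Hochberg across the seven between-group ANOVAs at a family-wise 0.05. Under Holm the smallest P value is compared with 0.05/7 = 0.0071, the next with 0.05/6 = 0.0083, and so on up to 0.05, stopping at the first failure. Holm needs no assumption about correlation; Hochberg needs independence or suitable positive dependence.

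Alternatively, if a source that predates the data already prespecified one outcome as primary, keep that one at 0.05, cite the source, and make the other six secondary. Without such a source, selecting a single primary now that recruitment has ended would itself be a late choice, so correction across the declared seven is preferable.

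If the by-group analysis has already been run, report all seven with adjusted P values and say when the variables and the adjustment were fixed.

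The cost is stricter thresholds, and so less power, for individual outcomes, plus a change of wording. No new patients or measurements are needed.

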**Discussion:**

This trial aims to explore the quantity-effect relationship between different acupuncture manipulations and their clinical effects. The results from this study may help explain the contradictory results found in acupuncture studies that practice different manipulations.

**Trial registration:**

Chinese Clinical Trial Registry: ChiCTR-RTRCC-12002675 (registered on 14 November 2012).

## Background

Vertigo is the main symptom of posterior circulation ischemia (PCI) [1]. Patients with vertigo resulting from posterior circulation ischemia (PCIV) are mainly middle-aged or older, and most patients are male [2]. The most common causes of PCI are atherosclerotic lesions, embolism, and small penetrating arterial disease, which lead to tissue function defects of the inner ear, brainstem, and cerebellum [2-5].

Traditional Chinese medicine (TCM) theorizes that vertigo is caused by a loss of nourishment in the upper orifices resulting from pathogenic wind, heat, phlegm, deficiency, or stasis. Vertigo is thought to be closely related to the liver, kidney, heart, and spleen [6]. Fengchi (GB 20) is one of the main acupoints used to treat vertigo, and acupuncture at Fengchi (GB 20) promotes the flow of qi and blood, pacifies the liver, and normalizes bile secretion [7]. Our previous study found that needling at Fengchi (GB 20) could improve cerebral blood flow in patients with PCIV [8].

Recent human and animal experiments have indicated that different needling manipulations could result in different effects through different physiological mechanisms [9,10]. However, few studies have investigated the influence of different needling directions and frequencies and their inherent mechanism of action.

We hypothesize that an ideal quantity of stimulation applied at Fengchi (GB 20) may induce an optimal effect in PCIV patients. This hypothesis is based on the quantity theory of acupuncture manipulation developed by academician [name], who stated, ‘acupuncture is an intervention for physical stimulation; so the quantity of stimulation including the intensity, frequency, duration, direction of the needle tip, and interval between intervention sessions may play a vital role in clinical outcomes. Just as with drugs, the effect of acupuncture is derived from the quantity of intervention. The optimal effect of acupuncture depends on the optimal stimulation quantity. Therefore, acupuncture intervention should be clearly quantified in clinical acupuncture research.’ In this study, we aim to explore whether different needling manipulations (direction and frequency) at Fengchi (GB 20) can influence the clinical effects of acupuncture via different physiological mechanisms. We also aim to investigate the most effective acupuncture parameters in patients with PCIV.

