### Rationale for acupoint selection and different manipulations of Fengchi (GB 20)

According to TCM theory, Fengchi (GB 20) is one of the main acupoints that can be used to help treat vertigo. Studies have demonstrated that acupuncture at Fengchi (GB 20) can affect cerebral blood flow [8,13].

Based on the quantity theory of acupuncture manipulation [14], differences in manipulations at Fengchi (GB 20) may induce different clinical effects. We selected different directions (the contralateral outer canthus or the Adam’s apple) and different frequencies (60 times per minute or 120 times per minute) to investigate our hypothesis. Needling manipulations will be performed manually by one experienced (more than 20 years) acupuncturist. Before conducting this trial, the acupuncturist received professional training to ensure the accuracy of needling replication.

The four manipulations used in this study are often used in clinical practice. Some studies state that the direction of acupuncture at Fengchi (GB 20) should be toward the contralateral outer canthus [15]. However, other studies acupuncture at Fengchi (GB 20) toward the Adam’s apple [16]. The two frequencies were chosen based on clinical experience.

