### Protocol for acupuncture manipulation

Sterile disposable stainless steel needles (length: 40 mm, diameter: 0.25 mm; Hwatuo, Suzhou Medical Supplies Factory Co., Ltd., Suzhou, China) will be used on patients. For the main acupoint, Fengchi (GB 20), each group will be needled with twisting for a minute. Group 1 will receive twirling with a frequency of 60 times per minute toward the contralateral outer canthus at a depth of 0.5 to 0.8 cun. Group 2 will receive twirling with a frequency of 60 times per minute toward the Adam’s apple at a depth of 0.5 to 0.8 cun. Group 3 will receive twirling with a frequency of 120 times per minute toward the contralateral outer canthus at a depth of 0.5 to 0.8 cun. Group 4 will receive twirling with a frequency of 120 times per minute toward the Adam’s apple at a depth of 0.5 to 0.8 cun (Figure 1). Additional points will be added based on individualized pattern diagnoses. For the retention of phlegm-dampness, we will add Fenglong (ST40), Zusanli (ST36), and Yinlingquan (SP9). For hyperactivity of Liver Yang, we will add Taichong (LR3) and Taixi (KI3). For deficiency of Kidney Yin, we will add Taixi (KI3), Zhaohai (KI6), and Neiguan (PC6). For blood stasis, we will add Hegu (LI4), Sanyinjiao (SP6), Yinxi (HT6), and Xuehai (SP10). For qi and blood deficiency, we will add Qihai (CV6), Zhongwan (CV12), Zusanli (ST36), and Laogong (PC8). After *de qi*, the needles will be retained for 20 minutes. Other interventions, such as moxibustion, cupping, and herbs will not be used. The participants will receive a total of 14 sessions over 3 to 4 weeks (3 to 4 sessions per week).

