We selected a pragmatic randomized controlled trial after an extensive discussion. Although both pragmatic and explanatory randomized controlled trials play important roles in the evaluation of health care interventions, the objectives and procedures of the two methods are different [23]. The primary objective of the explanatory trial is to determine whether acupuncture is better than placebo. Explanatory trials are an absolute proof for the validation of a therapeutic intervention [24]. To evaluate complex interventions such as acupuncture, the explanatory randomized controlled trial might not be an appropriate study design [25]. Instead, pragmatic randomized controlled trials can effectively investigate the overall impact of a group of treatments. Pragmatic trials can also provide a real comparison in clinical practice, which can provide a cost-effective analysis and can directly relate to policy. In pragmatic trials, the important question is whether the overall effect is worth the cost [23,26,27]. From a methodological perspective, explanatory RCTs demand rigorously controlled experimental conditions and the use of a placebo control [28]. Using a less rigidly controlled study design than those of explanatory RCTs, pragmatic trials can compare different interventions under actual clinical conditions, and placebo controls are not required [29]. However, pragmatic trials contain inherent deficiencies. Because of differences in needling techniques, treatments often include subtle variations, rendering the trials difficult to replicate [30]. To overcome this flaw, we will use a standardized acupuncture manipulation. The acupuncture treatments will be conducted by one acupuncturist with adequate clinical experience. Before conducting the trial, the acupuncturist received professional training to ensure accurate needle operation. Therefore, this trial should demonstrate adequate reproducibility.

This study is based on the quantity theory of acupuncture manipulation developed by [name]. This method aims to define and quantify acupuncture manipulation. The quantity theory of acupuncture manipulation has rendered the quantification of acupuncture more feasible and has contributed to the standardization, repeatability, and control of acupuncture studies. This method could be used to determine the optimal treatment method based on different parameters.

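### Two frequencies at one fixed duration, crossed with two unordered directions, can compare four settings but cannot show an ideal quantity or the shape of a quantity-effect curve

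*Protocol article*

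**What the plan says.** The Background of the protocol article states the hypothesis: "We hypothesize that an ideal quantity of stimulation applied at Fengchi (GB 20) may induce an optimal effect in PCIV patients". It then adds: "We also aim to investigate the most effective acupuncture parameters in patients with PCIV". The discussion paragraph of the Abstract gives the purpose as follows: "This trial aims to explore the quantity-effect relationship between different acupuncture manipulations and their clinical effects". The theory quoted in the Background takes a broad view of quantity: "the quantity of stimulation including the intensity, frequency, duration, direction of the needle tip, and interval between intervention sessions".

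The section on the rationale for acupoint selection gives the randomised factors: "different directions (the contralateral outer canthus or the Adam’s apple) and different frequencies (60 times per minute or 120 times per minute" per the four-group layout. On how the levels were picked, it says: "The two frequencies were chosen based on clinical experience". The section on acupuncture manipulation fixes the duration: "each group will be needled with twisting for a minute". All groups are scheduled for 14 sessions. The section on acupuncture groups says there is no sham arm and that the four settings will be compared directly. The analysis strategy specifies an ANOVA among the four groups for the between-group comparison, with significance at P below 0.05.

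**The concern.** A hypothesis about an ideal quantity is a hypothesis about a turning point: effect rises with quantity up to some level and then stops rising or falls. A trial with two levels of the only ordered factor has no information on such a turning point. Because duration is the same in every group, twirling rate and number of twirls also move together, although the quoted theory lists frequency and duration as separate components of quantity.

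Interpretation is what is at stake. A difference between 60 and 120 per minute could be written up as a quantity-effect curve, or the better setting as the optimum, when the data show only that one tested setting did better than another. A non-significant result could equally be taken to mean that quantity does not matter. In addition, one overall test across four groups does not say which factor is responsible for a difference, and it spends power on contrasts that may be empty.

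**Working it through.** **Inputs from the protocol article.** Frequencies 60 and 120 per minute; two directions; one minute in every group; four groups allocated 1:1:1:1; 144 participants, 36 per group, 20% withdrawal; significance level 0.05.

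**Assumptions.** A two-sided test, 80% power, standardised outcomes with common SD, and illustrative effects of 0.2 to 0.5 SD. The article gives no effect size, SD or power.

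**The plan's own figure.** 4 x 36 = 144, as stated. Evaluable per group: 36 x 0.8 = 28.8, taken as 29. The underlying formula cannot be reproduced, and the identifiability argument does not depend on it.

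**1. What the design identifies.** A model with intercept, frequency, direction and frequency x direction has 4 columns and rank 4 on 4 cells, so it is saturated. Adding frequency squared gives 5 columns and still rank 4. No curvature term can be estimated.

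To illustrate, set the mean effect to 0 at 60 per minute and 1 at 120. A curve a + bx + cx² through both points needs b = (1 - c(120² - 60²))/60 and turns at -b/(2c).
- c = 0: a straight line, with no turning point.
- c = -0.0005 (assumed): b = (1 + 5.4)/60 = 0.1067; peak at 0.1067/0.001 = about 107 per minute.
- c = +0.0005 (assumed): b = (1 - 5.4)/60 = -0.0733; minimum at 0.0733/0.001 = about 73 per minute.

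All three fit the two means exactly, so the trial cannot tell them apart.

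**2. Rate and amount.** Twirls per manipulation = rate x 1 minute, so 60 and 120. The two variables are identical in these data.

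**3. Detectable differences at 29 per group.** The multiplier is 1.96 + 0.84 = 2.80.
- Main effect, 58 v 58: 2.80 x √(2/58) = 0.52 SD.
- One pair, 29 v 29: 2.80 x √(2/29) = 0.74 SD; with the t distribution, 0.75 SD.
- Interaction as a difference of differences: 2.80 x √(4/29) = 1.04 SD.

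**4. Power for a pure frequency effect of 0.5 SD.**
- Frequency contrast: noncentrality 0.5/√(2/58) = 2.69; power about 76% by the t distribution (77% by the normal approximation).
- Four-group ANOVA: noncentrality 4 x 29 x 0.25² = 7.25 on 3 and 112 degrees of freedom; power 59%.

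**5. Ranking the four settings.** If one setting leads three equal ones by 0.2, 0.3 or 0.5 SD, simulation gives it the highest observed mean 58%, 73% or 93% of the time.

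**The case against.** The best defence is that the operational aim already fits the design. The Background also says the trial will explore whether direction and frequency influence clinical effect, and the section on acupuncture groups describes a direct comparison of four settings. Under the broad definition of quantity quoted in the Background, direction is part of quantity, so any comparison of the groups explores a quantity-effect relationship in that sense. Two levels can show whether effect differs with frequency. The best of the four tested settings can be named with fair reliability when it leads by 0.5 SD. The fixed one minute is stated openly, and the article never claims to separate rate from amount. Factorial contrasts may also be specified in an analysis plan that is not shown.

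Most of this stands, and it limits the point. It would be too strong to say that the trial can show nothing about quantity and effect. Counting direction as part of quantity does not, however, make it an ordered level on which a curve can be drawn. No analysis plan can estimate a turning point that the randomised arms do not contain.

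A reader might also infer that the article's closing conclusion asserts an optimum, from the Discussion sentence "This method could be used to determine the optimal treatment method based on different parameters". The documents do not support that. The sentence concerns the quantity theory in general, and the concluding paragraph speaks only of attempting to explore relative efficacies. The overreach lies in the hypothesis and the unrestricted aim.

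**Conclusion.** The point holds in a limited form. The ideal-quantity hypothesis, and the aim of finding the most effective parameters if read beyond the four settings, exceed what a 2x2 design with two frequencies, a fixed duration and unordered directions can identify. This part needs no numerical assumption.

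The mismatch between design and analysis is moderate: about 17 percentage points of power (76% against 59%) for a frequency effect of 0.5 SD that does not depend on direction, with 29 evaluable per group and a two-sided 0.05 level. Those figures rest on the assumed effect and on withdrawal at the stated 20%. No figure in the article is shown to be wrong. The article does not say that a null result would be read as equivalence; that is a risk to guard against in reporting.

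**What to change.** Recruitment ended in August 2014 according to the trial status section, so the arms cannot change. The analysis and the wording can.

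- **Analysis strategy.** Analyse the outcomes as a 2x2 factorial in place of only the four-group ANOVA. Report 120 v 60 twirls in one minute, direction, and their interaction, each with a 95% confidence interval. Say that rate and total twirls are not separable. If an analysis plan already specifies these contrasts, cite it.
- **Abstract and Background.** Limit the quantity-effect wording to this two-level contrast and the most-effective wording to the four tested settings. Mark the ideal-quantity hypothesis as the theory that motivates the trial, which the trial does not test.
- **Interpretation.** State that a non-significant difference is not evidence that the manipulations are equivalent.

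This needs no further patients or measurements. The price is a narrower headline claim. The interaction estimate will also be imprecise (detectable difference about 1.04 SD), so a main effect should be read beside the interaction's interval, and a non-significant interaction should not be taken as proof that the factors act independently.
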